#### 2.5.4. Calculation of the number of subjects

Assuming that the significance level (α) is 5% and the test power (1-β) is 80%, the number of subjects in each group is calculated so that the ratio of the 2 groups is 1:1.

$$\begin{array}{l} n=\frac{2\sigma^{2}{\left(Z_{1-\beta }+Z_{1-\frac{\alpha }{2}}\right)}^{2}}{d^{2}}=\frac{2\times 1.12^{2}{\left(Z_{0.8}+Z_{0.975}\right)}^{2}}{{\left(-1.15\right)}^{2}}\approx 15 \end{array}$$

The CP group is divided into the CONS, DISCEC, and FUSION groups, and CP non-applied group is also divided into the corresponding 3 groups. The minimum number of subjects required for this study is 15 per group, with a total of 90; however, considering the dropout rate (10%), a total of 102 subjects (17 per group) will be enrolled.

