##### 2.7.1.2. Secondary outcomes

For the CONS, DISCEC, and FUSION groups, we will evaluate whether the decrease in the VAS score of the CP group is statistically significant compared to that in the corresponding control group on day 1 of hospitalization and discharge.For the 3 treatment groups, we will evaluate whether the changes in the ODI, SF-36, and EQ-5D-3L scores in the CP group are statistically significant compared to those in the corresponding control group on day 1 of hospitalization and 4 weeks after discharge.For the 3 treatment groups, we will evaluate whether the changes in the ODI, SF-36, and EQ-5D-3L scores in the CP group are statistically significant compared to those in the corresponding control group on day 1 of admission and discharge.The average length of hospitalization will be compared between the CP group and the corresponding control group for all 3 treatment groups.After the patient is discharged from the hospital, a questionnaire for employee satisfaction will be used to evaluate the satisfaction of doctors, nurses, and hospital staff with the application of CP.After the patient is discharged from the hospital, the patient’s satisfaction with the medical services will be investigated through a questionnaire, and the satisfaction scores between the CP group and the corresponding control group will be compared.We will compare the consultation waiting time between the CP group and the corresponding control group.In addition to the fixed oral preparations and intravenous infusions, the amount of pro re nate (Pro Re Nate) analgesic used for pain will be investigated and compared between the CP group and the corresponding control group.The CP application rate and completion rate will be analyzed in the 3 groups.

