##### 2.8.1.2. Secondary outcome analysis

The differences in VAS scores measured on day 1 of hospitalization and at 4 weeks after discharge in each treatment group will be analyzed with a linear model assuming a normal distribution. In the analysis model, including the treatment group (CP and control groups), age, sex, type of insurance related to back pain, region of residence, Charlson Comorbidity Index (CCI), surgery status, and hospitalization record as covariates and factors, we will evaluate if the VAS score reduction in the CP group is statistically significant compared to that in the control group. If the normality of the VAS scores is not satisfied, we will use a sandwich estimator or perform a nonparametric statistical analysis.The differences in VAS scores measured on the day of hospitalization and discharge in each treatment group will be analyzed with a linear model assuming a normal distribution. In the analysis model, including the treatment group (CP and control groups), age, sex, type of insurance related to back pain, region of residence, CCI, surgery status, and hospitalization record as covariates and factors, we will evaluate if the VAS score reduction in the CP group is statistically significant compared to that in the control group. If normality of the VAS scores is not satisfied, we will use a sandwich estimator or perform a nonparametric statistical analysis.The differences in ODI, SF-36, and EQ-5D-3L scores measured on day 1 of hospitalization and 4 weeks after discharge in each treatment group will be analyzed with a linear model assuming a normal distribution. In the analysis model, including the treatment group (CP and control groups), age, sex, type of insurance related to back pain, region of residence, CCI, surgery status, and hospitalization record as covariates and factors, we will evaluate if the VAS score reduction in the CP group is statistically significant compared to that in the control group. If normality of the ODI, SF-36, and EQ-5D-3L scores is not satisfied, we will use a sandwich estimator or perform a nonparametric statistical analysis.The differences in ODI, SF-36, and EQ-5D-3L scores measured on the day of hospitalization and discharge in each treatment group will be analyzed with a linear model assuming a normal distribution. In the analysis model, including the treatment group (CP and control groups), age, sex, type of insurance related to back pain, region of residence, CCI, surgery status, and hospitalization record as covariates and factors, we will evaluate if the VAS score reduction in the CP group is statistically significant compared to that in the control group. If normality of the ODI, SF-36, and EQ-5D-3L scores is not satisfied, we will use a sandwich estimator or perform a nonparametric statistical analysis.The average length of hospital stay in the CP group and control group will be compared by a 2-sample *t* test. If normality is not satisfied, the Wilcoxon rank-sum test will be performed.After patient discharge, we will perform the χ^2^ test or Fisher exact test for the test and control groups (CP applied and CP non-applied group) for staff satisfaction data obtained through a questionnaire.After patient discharge, we will perform a homogeneity test for the test and control groups (CP applied and CP non-applied groups) to evaluate patient satisfaction using the data obtained from the questionnaires.The consultation waiting time will be compared between the CP and control groups was compared using a 2-sample *t* test. If normality is not satisfied, the Wilcoxon rank-sum test will be performed.To compare the additional amount of pro re nate analgesic consumed between the CP and control groups, a 2-sample *t* test will be used. If normality is not satisfied in the normality test for additional analgesic use, the Wilcoxon rank-sum test will be performed.We will perform ANOVA (analysis of variance) to compare the average CP application and completion rates in the CONS, DISCEC, and FUSION groups of the CP group.

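### The hypothesis sentence in both ODI, SF-36 and EQ-5D-3L analysis items names the VAS reduction, contradicting the modelled response and the outcome definition

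*Protocol article*

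**What the plan says.** Section 2.7.1.2 (Secondary outcomes) sets the aim for the three patient-reported instruments. For each treatment stratum, "we will evaluate whether the changes in the ODI, SF-36, and EQ-5D-3L scores in the CP group are statistically significant" against the corresponding control group. This is stated once for day 1 to 4 weeks after discharge and once for admission to discharge.

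Section 2.8.1.2 (Secondary outcome analysis) has one item for each interval. The first opens with "The differences in ODI, SF-36, and EQ-5D-3L scores measured on day 1 of hospitalization and 4 weeks after discharge in each treatment group will be" analysed by a linear model. The second opens with "The differences in ODI, SF-36, and EQ-5D-3L scores measured on the day of hospitalization and discharge in each treatment group will be analyzed", also by a linear model. Both models include group (CP or control), age, sex, type of insurance, region of residence, comorbidity index, surgery status and hospitalisation record. Both items then state what is to be evaluated, and in both the text running into the fallback is "the VAS score reduction in the CP group is statistically significant compared to that in the control group. If normality of the ODI". Both close with "If normality of the ODI, SF-36, and EQ-5D-3L scores is not satisfied, we will use a sandwich estimator or perform a nonparametric statistical analysis".

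The two items just before these deal with VAS over the same two intervals. They carry the same hypothesis sentence, which is correct there.

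**The concern.** Within each item, the response and the fallback name one set of outcomes and the hypothesis names another. The hypothesis also disagrees with section 2.7.1.2, which the item is meant to carry out. As a result, the analysis section states the VAS hypothesis four times in a row and never states a hypothesis for disability or quality of life.

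A plan should fix the decision statement for each outcome before the data are seen. Here a programmer or later reader has to decide which part of the item governs. ODI, SF-36 and EQ-5D-3L are the function and quality-of-life outcomes of the study, so the statement should be right for them.

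The covariate list shared by these items also omits the day-1 value of the outcome being analysed. Patients enter the CP or control group by their own choice (sections 2.1 and 2.3), so day-1 scores may differ between the groups.

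**Working it through.** The point concerns wording, so the check sets the texts side by side.

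| Element | Outcome named, 4-week item | Outcome named, discharge item |
|---|---|---|
| Aim (2.7.1.2) | change in ODI, SF-36, EQ-5D-3L | change in ODI, SF-36, EQ-5D-3L |
| Model response (2.8.1.2) | ODI, SF-36, EQ-5D-3L | ODI, SF-36, EQ-5D-3L |
| Group term (2.8.1.2) | CP v control | CP v control |
| Hypothesis (2.8.1.2) | **VAS reduction** | **VAS reduction** |
| Normality fallback (2.8.1.2) | ODI, SF-36, EQ-5D-3L | ODI, SF-36, EQ-5D-3L |

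1. *Which element is wrong?* In each column the aim, the response and the fallback agree, and only the hypothesis differs. It matches the sentence in the two VAS items above it. A copying slip is the most plausible explanation.

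2. *Can the test be recovered?* Yes. A linear model with the ODI change as response and a CP/control term gives a between-group test of ODI through that term. The same holds for SF-36 and EQ-5D-3L. No VAS test can come out of such a model.

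3. *How many contrasts does the sentence cover?* Counting SF-36 as one outcome, 3 instruments x 2 intervals x 3 strata (CONS, DISCEC, FUSION) = 18. All 18 have a mis-stated hypothesis. By step 2, the number left without a recoverable test is 0.

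4. *Does it touch the sample size?* No. The only calculation (section 2.5.4) is for VAS, with d = -1.15, SD = 1.12, two-sided alpha 5% and power 80%: n = 2 x 1.12² x (0.842 + 1.960)² / 1.15² = 14.89, rounded up to 15 per group. Then 15 / 0.90 = 16.7, rounded up to 17, and 17 x 6 = 102. The plan's figures reproduce, and correcting the sentences changes none of them.

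5. *Does it touch the economic analysis?* No. Section 2.7.2.1 separately plans the comparison of QALYs from the 4-week EQ-5D score.

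6. *Is the day-1 value available?* Yes. The response is a difference from day 1 or admission, so the starting score must be collected to compute it.

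**The case against.** The strongest case against is that this is an editorial slip. Response, group term, covariates and fallback all name the right outcomes, section 2.7.1.2 states the comparison in full, and no competent analyst would be misled. Much of this stands, and it rules out several stronger inferences that a reader might draw:

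- *That these outcomes have no test of their own.* The documents do not support this. The group term in each model is the test, and section 2.7.1.2 gives the decision statement.
- *That VAS would be tested again under another label.* The models described have no VAS response.
- *That the plan applies the wrong direction to SF-36 and EQ-5D-3L.* In section 2.8.1.2 the word for a fall is attached only to VAS, and section 2.7.1.2 uses a neutral word for the other instruments. Direction matters only for the correction: replacing the outcome name and keeping the word for a fall would create an error for SF-36 and EQ-5D-3L, where higher is conventionally better.
- *That the utility behind the QALY goes unanalysed.* Section 2.7.2.1 covers it independently.

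The objection does not make the text correct. The error stands twice in the operative analysis section and contradicts both the rest of its own item and the outcome definition. It is not an omission that article condensation or an unseen analysis plan would explain, because the sentence is present and names the wrong endpoint.

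It can also be said that adjusting for the day-1 value is a separate modelling choice. That is fair: the contradiction stands without it. It is offered as an improvement to the same two items, justified by the non-randomised allocation and by data already in hand.

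**Conclusion.** The point holds as a mis-stated hypothesis in two places, not as missing tests. Two sentences in section 2.8.1.2 name VAS where ODI, SF-36 and EQ-5D-3L belong. They govern 18 planned secondary contrasts, all of which remain recoverable from the model description and section 2.7.1.2. The primary outcome, the sample size of 102, power, alpha and the QALY analysis are unaffected.

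The conclusion rests on reading the sentence as copied from the VAS items, which the agreement of every other element supports. The count of 18 assumes that SF-36 is analysed as a single outcome; separate SF-36 scales would raise it. It should be corrected before analysis, but it does not threaten the study.

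**What to change.** In both ODI, SF-36 and EQ-5D-3L items of section 2.8.1.2:

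1. Replace the reference to the VAS reduction with the change in the ODI, SF-36 and EQ-5D-3L scores, so that the hypothesis matches section 2.7.1.2. State the favourable direction for each instrument. Under conventional scoring, which the article does not spell out, this is a decrease for ODI and an increase for SF-36 and EQ-5D-3L.
2. Add the outcome's own day-1 (admission) value to the covariate list of each model.

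The first change costs two sentences. The second needs no new data and uses one degree of freedom per model, in strata of 2 x 15 = 30 to 2 x 17 = 34 patients. Neither alters the sample size. Any statistical analysis plan should carry the same wording.

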## 2. Materials and methods

### 2.1. Study design

This single-center prospective observational study will be performed at Kyung Hee University Medicine Hospital and Kyung Hee University Korean Medicine Hospital to analyze the effectiveness, economy, and safety of using an integrated medical service CP in patients with L-HNP. The patients will be divided into groups that apply critical pathway of integrative medical services and those who do not.

From among the patients who agree to participate in the study, those who meet the inclusion criteria will be registered as research subjects. Among them, those who agree to participate in the integrated medical service CP will be assigned to the test group (integrated medical service CP applied group) and those who do not will be assigned to the control group (integrated medical service CP non-applied group). Both groups are further divided into a conservative treatment (CONS) group, an open discectomy (DISCEC) group, and an interbody fusion (FUSION) group based on the main medical treatment. In the test group, inpatient treatment will be administered according to the pathway of the prescribed protocol. In the control group, inpatient treatment will be administered based on the treating doctor’s judgment, without a prescribed pathway. The test group patients will be discharged after being hospitalized for a set hospitalization date, whereas in the control group, the time of discharge will be determined according to the judgment of the clinician. The study will be completed when the patients are evaluated during an outpatient visit to the Department of Neurosurgery of Kyung Hee Medical Center 4 weeks after discharge.

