### 2.4. Clinical trial plan and critical pathway schedule

Among patients with lumbar intervertebral disc herniation visiting the Neurosurgery outpatient department of Kyung Hee Medical Center, patients with a VAS score of 7 or higher who require hospitalization can consent to participate in this study. Following patient consent, the doctors and research nurses will screen the patients according to the inclusion and exclusion criteria, enroll those who pass the screening, and confirm the participants intention to receive treatment using an integrated medical service CP. Depending on their intention to participate in the CP application, participants will be classified into the test or control group. Upon admission, the patients will be assigned to the CONS group, DISCEC group, and FUSION groups according to the judgment of the medical staff. The test group will receive inpatient treatment according to a previously developed integrated medical service CP plan, and the control group will receive inpatient treatment according to the clinician’s judgment without a set protocol. The study will be deemed complete when all patients will be evaluated during an outpatient visit to the Neurosurgery Department of Kyung Hee Medical Center 4 weeks after discharge.

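### Staff satisfaction is defined as satisfaction with applying the critical pathway but is tested between pathway and non-pathway patient groups, so outcome and test do not match

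*Protocol article*

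**What the plan says.** Section 2.7.1.2 defines the outcome: after discharge, "a questionnaire for employee satisfaction will be used to evaluate the satisfaction of doctors, nurses, and hospital staff with the application of CP". It mentions no control group for this item. The next item, patient satisfaction, does: "the satisfaction scores between the CP group and the corresponding control group will be compared".

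Section 2.8.1.2 then gives the analysis of the staff item: "we will perform the χ^2^ test or Fisher exact test for the test and control groups (CP applied and CP non-applied group) for staff satisfaction".

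Section 2.4 describes what the groups are. On assignment: "Depending on their intention to participate in the CP application, participants will be classified into the test or control group". On treatment: "the control group will receive inpatient treatment according to the clinician’s judgment without a set protocol". Section 2.1 adds that this is a single-centre study.

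The abstract lists medical staff satisfaction among the data to be collected, without tying it to the CP.

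**The concern.** A two-group test needs a value of the same outcome in both groups. Satisfaction with applying the CP exists only where the CP is applied. In the control group either there is nothing to record, or staff answer a different question from the one defined.

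The unit is a second difficulty. Chi-square and Fisher tests treat each response as coming from a separate, independent subject who belongs to one group. The respondents here are staff, and the plan places no staff member in either group.

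At stake is a p value on how acceptable the CP is to staff that would have no clear interpretation. Nothing else in the trial depends on it.

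**Working it through.** **Step 1. Outcome against test.** The plan's own text, side by side:

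| Item | Defined as (2.7.1.2) | Analysed as (2.8.1.2) | Match |
|---|---|---|---|
| Patient satisfaction | CP against control | CP against control | yes |
| CP application and completion rates | the three treatment groups | CP group only | yes, a CP-only measure kept within the CP group |
| Staff satisfaction | with application of the CP, no control named | CP against control | no |

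The plan treats another CP-only measure consistently. The staff item as defined is of the same kind but is given a between-arm test.

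**Step 2. The unit.** A staff response can be labelled CP or control only through the patient it refers to. There are two possibilities:

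- Each staff member answers once. That person may have cared for patients in both groups and belongs to neither, so the test has no grouping variable.
- Staff answer after each discharge. The grouping exists, but forms from one person are correlated and the unpaired test ignores this.

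The article does not say which applies. The unpaired test fits neither.

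**Step 3. Size of the dependence problem, if forms are repeated.** The plan gives no figure for this outcome. The only design figure is the VAS sample size, which reproduces: 2 × 1.12² × (0.842 + 1.960)² / 1.15² = 14.89, rounded up to 15; 15 / 0.9 = 16.7, rounded up to 17; 6 × 17 = 102. Each arm therefore has 3 × 17 = 51 patients.

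Inputs that are assumptions, not in the document: one form per patient (m = 51 per arm), a yes/no item with 60% satisfied, K = 5, 10 or 20 raters, forms spread evenly over raters, within-rater correlation ρ = 0.1 to 0.5, and no true difference.

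The test takes the variance of the difference in proportions as 2p(1 − p)/m. The true variance is that value multiplied by:

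- 1 − ρ, if the same raters score both arms equally, because the rater effect cancels. For ρ = 0.1, 0.3, 0.5 this is 0.9, 0.7, 0.5. The test is conservative.
- 1 + (m/K − 1)ρ, if each arm has its own raters. For K = 5 and ρ = 0.1 this is 1 + 9.2 × 0.1 = 1.92. The test is anti-conservative.

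Simulated rejection rate of a nominal 5% chi-square test without continuity correction (beta-binomial raters, 20,000 trials per setting):

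| Raters K | ρ | Same raters in both arms | Different raters in each arm |
|---|---|---|---|
| 5 | 0.1 | 4.5% | 17.5% |
| 5 | 0.3 | 2.7% | 33.2% |
| 5 | 0.5 | 1.3% | 43.4% |
| 10 | 0.1 | 4.5% | 10.4% |
| 10 | 0.3 | 2.5% | 20.4% |
| 10 | 0.5 | 0.9% | 27.9% |
| 20 | 0.1 | 4.2% | 7.6% |
| 20 | 0.3 | 2.3% | 11.5% |
| 20 | 0.5 | 0.9% | 15.4% |

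For K = 10 and 20, K counts the raters in both arms together in the shared case, and the raters per arm in the other. The Fisher test was not simulated.

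**The case against.** The questionnaire is not shown. Its name in section 2.7.1.2 is general, and the abstract's label carries no reference to the CP. If the form asks about satisfaction with care overall, it can be completed for patients with and without the CP, and the loose wording would lie in the outcome definition rather than the test. This stands. The documents show a mismatch to be reconciled; they do not show that a comparison with usual care is impossible in principle.

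It is also fair that team size and forms per staff member are not stated, and that such detail is often left to a full protocol or analysis plan. The dependence argument is therefore conditional. Its absence from the article is not the point; the point is that the named test does not fit the named outcome. A general item would cure the first difficulty but not the second, since staff would still be unassigned and the test unpaired.

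A reader might infer that the planned test would give many false positives, as in the last column of the table. The documents do not support that. Those figures need different staff in the two arms, whereas this is one centre, recruiting through one neurosurgery department, with groups formed by patient choice. Shared raters are the more natural reading, and there the test errs towards too few rejections. Partial overlap would fall between the columns, and if every form came from a different person the dependence would vanish.

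**Conclusion.** The mismatch holds on the text alone: the staff outcome concerns application of the CP, the test requires control-group values, and the control group has no CP. Which of the two sections expresses the intention is open.

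The loss of independence is likely but inferred. If raters are shared equally between arms, the real level of the nominal 5% test is about 1% to 5% under the assumptions listed, with a loss of power. Inflation arises only to the extent that different staff serve the two arms.

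The point should be corrected, but it is limited to one secondary outcome. The primary VAS comparison and the sample size of 102 are untouched.

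**What to change.** Reconcile sections 2.7.1.2 and 2.8.1.2 by stating what the item rates.

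- If it rates the CP: remove the chi-square or Fisher comparison and report satisfaction descriptively with confidence intervals, with the staff member as the unit.
- If a contrast between CP and usual care is wanted: define the item with identical wording for both, have the same staff rate each, and analyse within rater by McNemar, Wilcoxon signed-rank or a model with a rater effect.

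The cost is a change of wording and, for the second option, a rater identifier on each form. The sponsor gives up the unpaired between-arm p value.

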#### 2.5.1. Average change in the VAS score

The average change in VAS was calculated as 2.27 to 6.14 = −3.87 in the treatment group and 3.37 to 6.09 = −2.72 in the control group. Therefore, the difference in the change in the VAS score before and after treatment between the 2 groups was d=−3.87 to (−2.72) = −1.15.

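### Patient satisfaction scores are to be compared between groups, but the analysis names only an undefined homogeneity test, which in its usual chi-square sense ignores the order of the scores and gives no direction or size of difference

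*Protocol article*

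**What the plan says.** The secondary outcomes (2.7.1.2) state that patients complete a satisfaction questionnaire after discharge and that "the satisfaction scores between the CP group and the corresponding control group will be compared".

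The matching item in the secondary outcome analysis (2.8.1.2) reads "we will perform a homogeneity test for the test and control groups (CP applied and CP non-applied groups) to evaluate patient satisfaction". It does not name the statistic, the response scale, the number of answer levels or the quantity to be reported.

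Two neighbouring items in 2.8.1.2 bear on how to read it:
- The item just before it assigns a chi-square test or "Fisher exact test for the test and control groups (CP applied and CP non-applied group) for staff satisfaction data obtained through a questionnaire".
- Length of stay, consultation waiting time and as-needed analgesic use each get a two-sample t test, with a rank test as fallback. For the first two the wording is "If normality is not satisfied, the Wilcoxon rank-sum test will be performed", and analgesic use has an equivalent rule.

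**The concern.** The outcome section speaks of scores, which have an order and usually a level that can be higher or lower. A chi-square test of homogeneity asks a different question: whether every answer category has the same probability in both groups. Shuffling the category labels would not change its result. It therefore cannot say which group is more satisfied or by how much, and it spreads its power over every way in which two distributions can differ.

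Two things are at stake. A real gain in satisfaction is more likely to be missed than under the methods the plan uses for its other numeric secondary outcomes. And a significant result could not be read as CP patients being more satisfied, because a wider spread of answers around the same average can also produce it. The introduction names better patient satisfaction among the reasons for bringing CPs into Korean medicine, so readers will look at this result.

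**Working it through.** **The plan's own figure.** The only sizing is for the primary VAS outcome (2.5.1 to 2.5.4): a difference of 1.15, SD 1.12, two-sided 5% and 80% power.

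n = 2 × 1.12² × (0.842 + 1.960)² / 1.15² = 2 × 1.2544 × 7.849 / 1.3225 = 14.89, rounded up to 15.

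With 10% dropout, 15 / 0.9 = 16.67, rounded up to 17, and 6 × 17 = 102. This agrees with the plan: "considering the dropout rate (10%), a total of 102 subjects (17 per group) will be enrolled". No effect size or power is stated for satisfaction. The sizes that matter here are 15 to 17 per arm within a treatment group, or 3 × 15 = 45 to 3 × 17 = 51 per arm if the three treatment groups are pooled.

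**Assumptions not in the documents.** The homogeneity test is taken as Pearson's chi-square test on a 2 × K table. K, the number of answer levels, is varied from 2 to 11. The effect is a shift in score level.

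**Power for a shift, large-sample.** A one-degree-of-freedom location test has 80% power at 5% when its noncentrality is (0.842 + 1.960)² = 7.849. If the location score captures the whole shift, the homogeneity test has the same noncentrality but spreads it over K − 1 degrees of freedom. Its power is the probability that a noncentral chi-square variable with K − 1 degrees of freedom and noncentrality 7.849 exceeds the 5% critical value.

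| Levels K | df | Critical value | Power | Loss from 80%, points |
|---|---|---|---|---|
| 2 | 1 | 3.84 | 80% | 0 |
| 3 | 2 | 5.99 | 71% | 9 |
| 4 | 3 | 7.81 | 64% | 16 |
| 5 | 4 | 9.49 | 60% | 20 |
| 7 | 6 | 12.59 | 52% | 28 |
| 11 | 10 | 18.31 | 43% | 37 |

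**Power for a shift, simulated** (4000 runs per case, proportional-odds shift, Wilcoxon as comparator).

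| Levels | n per arm | Odds ratio | Homogeneity | Wilcoxon |
|---|---|---|---|---|
| 2 | 17 | 4 | 45% | 45% |
| 3 | 17 | 4 | 41% | 52% |
| 5 | 17 | 4 | 34% | 58% |
| 7 | 17 | 4 | 24% | 59% |
| 11 | 17 | 4 | 17% | 59% |
| 5 | 45 | 3 | 58% | 81% |

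The loss shrinks when the effect is large enough for both tests to succeed. With 5 levels, 51 per arm and an odds ratio of 6, it is 2 points.

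**Equal averages, different spread.** Take five levels scored 1 to 5. One group has probabilities 0.05, 0.20, 0.50, 0.20, 0.05 and the other 0.20 for each level. Both means are 3. The variances are 2 × (0.05 × 4 + 0.20 × 1) = 0.8 and 2 × (0.20 × 4 + 0.20 × 1) = 2.0. The simulated rejection rates at 5% are:

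| n per arm | Homogeneity | Wilcoxon | t test |
|---|---|---|---|
| 17 | 39% | 6% | 5% |
| 45 | 88% | 6% | 5% |

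With 2 levels this cannot happen, because equal averages then mean equal distributions.

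**The case against.** The best defence is that the outcome section says only that scores will be compared. It states no null hypothesis, no mean and no direction, although the same list writes of an average for length of stay. Asking whether two answer distributions differ is a legitimate comparison, and rejecting on unequal spread is then what the test is for. This stands in part: the documents do not state a null of equal score level, so the point is a poor match of method to outcome rather than a flat contradiction.

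Second, the chi-square reading is inferred. The plan names chi-square or Fisher for staff and then uses a different term for patients, so something else may have been meant. That also stands. But the other common meaning, homogeneity of variances, would not address satisfaction level at all and would fit the outcome less well. The point is also more than detail left to a fuller document: the article does name a method, and it differs from the one it uses for its other numeric secondary outcomes.

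Third, a reader might infer that the plan loses more than 20 points of power. The documents do not support that. They give neither scale nor effect size, and a loss of that order needs roughly five or more levels and a mid-range effect. With binary items there is no loss and the chi-square test is suitable.

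**Conclusion.** The concern holds in a limited form. The plan sets out to compare patient satisfaction scores and then names an undefined test which, in its most natural reading, ignores their order and reports neither direction nor size. That conclusion rests on the chi-square reading and on a score with three or more levels.

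The cost in power depends on assumptions that the documents do not settle. It runs from 0 points with 2 levels to about 37 with 11 at the 80%-power shift, and is smaller for very large effects. The 39% rejection rate with equal averages belongs to one assumed pair of 5-level distributions; it shows what can happen and does not forecast this study. No power was claimed for satisfaction and the primary VAS comparison is untouched, so this is a cheap improvement to a secondary analysis.

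**What to change.** In 2.8.1.2, replace the patient-satisfaction item with wording such as: Patient satisfaction scores will be compared between the CP group and the corresponding control group within each treatment group by the Wilcoxon rank-sum test (two-sample t test for an approximately normal summed score), and the difference will be reported with a 95% confidence interval. Any binary or nominal items will be compared by the chi-square or Fisher exact test.

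This brings the item into line with the other numeric secondary outcomes and with the comparison against the corresponding control group set out in 2.7.1.2. It costs one or two sentences, with no new data or patients. The downside is that a difference only in the spread of answers is no longer formally tested; a frequency table of the answers by group would still show it.
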